**Fig. 1 Fig1:**
[figure not shown]
Study of active neighborhoods in Detroit (StAND) conceptual diagram of study exposures and outcomes. Items enclosed in the dotted oval will be measured in this study

The study was approved by the Michigan State University’s Institutional Review Board (IRB Approval #STUDY00000587; date 03/21/2019). The study was registered with OFS (osf.io/surx7) and successfully tested in a pilot study ([name], [name], [name], [name], [name], [name], et al: Feelings of safety during daytime walking: Associations with mental health, physicial activity and cardiometabolic health in two high vacancy, low-income neighborhoods in Detroit, Michigan, in review) [43]. The protocol was completed using the TREND guidelines [44].

### Participants

Participants are adults who reside in a study park’s zone of influence, which is deemed to be 0.5 km (0.31mi), which is an approximate 15-min walk to the park and also a reasonable maximum distance for hearing birdsong in an urban setting [45]. Participants will be recruited from within a 16-cell grid (120m^2^/cell) around each park. Thus, the unit of measurement is the individual, but the unit of assignment-to-intervention is neighborhood. We conducted a pilot study in two neighborhoods in 2018 (*n* = 67 participants enrolled) and received funding at the end of the summer in 2019, yielding a truncated field season (*n* = 145 participants). The first full field season for this study will be 2020. To recruit participants, we mail postcards and conduct recruitment activities (e.g., information booths) in each neighborhood. Field staff then visit homes in each study neighborhood to brief potential participants on the study, request participation, and screen for inclusion. We recruit only one English-speaking male or female (≥ 18y) without mobility issues per household, which is at the household’s discretion. To ensure participant comprehension and confirm contact information, we use an electronic text message to finalize enrollment. Participants are then instructed on the correct usage of the accelerometer (Actigraph GT3X), Global Positioning System (GPS) device (Canmore) and cortisol sample collection and instructed that a study shuttle will take them to their scheduled health appointment in our study office. The target total sample is 450 adults to be recruited and retained. To retain participants, we will employ a set of strategies including: 1) sending holiday cards with neighborhood-level results; 2) sending birthday cards; and 3) sending periodic, brief surveys through StANDApp.

### Sample size

Assuming a longitudinal panel design, sample size assessments for the study are based on achieving 82% power to test the hypotheses. The effect measure is a difference-in-differences (DID) — in hypotheses 1–3, i.e., the expected change in PA from baseline to three-years post-restoration in INT parks compared to the corresponding change in CNT parks. Hypotheses 3–6 concern a DID in stress outcomes. A review of the literature on PA [46] and cortisol [47] suggests an effect size (EF) of 0.35 could be posited. Accordingly, we calculate our sample size requirements to detect an EF of 0.35 or better with 82% power. Two other design features are: a serial correlation *r* between repeated measures over time and intra-class correlation (ICC) *ρ* for clustering within neighborhood parks. In community-intervention studies such as ours, *ρ* is small [48–51]. Plausible values from the literature and our own experiences, suggest *r* ≥ 0.35 and *ρ ≤* 0.004. With a total of nine parks (4 INT, 5 CNT), we will need a sample of 450 participants, or 50 per park, to detect EF = 0.35 with 82% power, based on a two-sided test at significance level 5%. Because attrition is expected over the study period, we will recruit a total of 620 participants at t = 0 (baseline) to account for attrition of 15% at t = 1 and another 10% at t = 2 and 5% at t = 3. Our sample size assessment may also be deemed conservative as it does not account for potential influence of fixed covariates, which should increase precision on the intervention effect estimate by reducing residual variance resulting in a positive effect on power.

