We adopt a regression-based approach to multivariable modeling that addresses features of clustering of participants within parks and correlation over time in repeated assessments. Repeated measures ANOVA, or more apropos, generalized linear (mixed) models (GLMM) will be used [135–137]. Denote by $$ {\mathit{\mathsf{Y}}}_{\mathit{\mathsf{it}}} $$ an outcome in the *i*-th participant in the *h-*th park assessed at time *t*. It is assumed that an individual is primarily exposed to one park. Generally, outcomes are assessed at baseline and at least 3 additional time-points, denoted t = 0, 1, 2, 3. Our hypotheses concern the expected response: $$ {\textsf{g}}\left({\mu}_{{\textsf{hi}\textsf{t}}}\right)={\mathbf{\textsf{x}}}_{{\textsf{it}}}^{\prime}\beta +\mathbf{\textsf{z}}{\hbox{'}}_{{\textsf{ht}}}{\mathbf{\textsf{b}}}_{{\textsf{hi}}} $$ .The GLMM is expressed as $$ {\textsf{g}}\left({\mu}_{{\textsf{hi}\textsf{t}}}\right)={\mathbf{\textsf{x}}}_{{\textsf{it}}}^{\prime}\beta +\mathbf{\textsf{z}}{\hbox{'}}_{{\textsf{ht}}}{\mathbf{\textsf{b}}}_{{\textsf{hi}}} $$ with link function *g* appropriate to type of outcome (continuous, categorical, count, ordinal) random effects $$ {\mathbf{\textsf{b}}}_{{\textsf{hi}}} $$ to capture serial correlation within participant measures and clustering [138]. The covariates $$ {\mathbf{\textsf{x}}}_{{\textsf{hit}}} $$ are participant characteristics, some of which are time-invariant such as the aforementioned sociodemographic variables; $$ {\mathbf{\textsf{z}}}_{{\textsf{ht}}} $$ are characteristics of park *h* at time *t.* Minimally, the predictor variables are: a single indicator for GROUP, with CNT as referent, three indicators for TIME, corresponding to t = 1, 2, 3 with baseline t = 0 as referent, and GROUP×TIME interactions. A measure of exposure to environmental stimuli is included in participant characteristics. The GLMM allows us to formulate and test hypotheses on functions of the regression parameters β, including: i) point-in-time comparison between INT and CNT, e.g., at each follow-up year; ii) time-averaged comparison between INT and CNT; iii) within group comparison for change over time; and iv) change in INT compared to the corresponding change in CNT via DID. SAS Software v9.4 (Analytics 15.1 or higher) will be used for statistical analyses.

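### With the effect size in outcome-SD units and the plan's bounding r and ρ, power on the 7 degrees of freedom of nine assigned neighborhoods is about 68–72%, not 82%, and the claim also covers hypotheses that are not difference-in-differences

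*Protocol article*

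**What the plan says.** The Sample size section opens by saying that "sample size assessments for the study are based on achieving 82% power to test the hypotheses", and takes the DID from baseline to three years as its effect measure. It says that the literature "suggests an effect size (EF) of 0.35 could be posited" and that plausible values "suggest *r* ≥ 0.35 and *ρ ≤* 0.004". From these it derives 450 participants, 50 in each of nine parks (4 INT, 5 CNT), for 82% power with a two-sided 5% test. It names no formula, no reference distribution or degrees of freedom, and no SD that standardises the effect size.

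The Participants section says that "the unit of measurement is the individual, but the unit of assignment-to-intervention is neighborhood". The Abstract gives individuals as the unit of analysis.

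The Statistical analysis section writes a generic mixed model with GROUP, TIME and GROUP×TIME as the minimum fixed terms, and random effects "to capture serial correlation within participant measures and clustering".

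On scope, the Sample size section first ties the DID in physical activity to Hypotheses 1–3 and then says "Hypotheses 3–6 concern a DID in stress outcomes".

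**The concern.** When condition is assigned to whole neighborhoods, park-level change over time is part of the error of the DID, and that error is estimated from nine units in two groups, so on 9 − 2 = 7 df. The two-sided 5% critical value is then 2.365 instead of 1.96. The Sample size section evidently counts park variance, since without it the power would be about 90%. However, the figure it reaches matches a reference that ignores how few parks estimate that variance. If so, the chance of missing an effect of 0.35 on the primary outcome is near 30% instead of 18%. The section calls its assessment conservative because covariates are not counted; leaving out park-level df errs in the other direction.

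A separate problem is scope. The Objectives and the hypothesis-by-hypothesis analyses treat Hypotheses 3, 5 and 6 as associations with exposures or with activity level. Hypothesis 3 replaces the binary group predictor with continuous exposures. Power for a two-group DID says nothing about those tests. Hypothesis 3 is also counted under both physical activity and stress, although it concerns physical activity.

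**Working it through.** **Inputs.** From the Sample size section: effect size 0.35, r = 0.35 and ρ = 0.004 (the stated bounds), m = 50 per park, 4 versus 5 parks, two-sided 5%. The 450 is the year-3 number: 620 × 0.85 × 0.90 × 0.95 = 450.6. Assumption: the effect size is in outcome-SD units.

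**Variance of the DID.** With r_g the correlation over time of a park's effects (not given in the protocol, so bracketed at 0 and 0.35):

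Var = [2(1 − r)(1 − ρ)/50 + 2ρ(1 − r_g)] × (1/4 + 1/5)

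- r_g = 0.35: (0.025896 + 0.0052) × 0.45 = 0.01399, SE 0.1183, ratio 0.35/SE = 2.959. This equals the usual design effect, 1 + 49 × 0.004 = 1.196, applied to 2(1 − r).
- r_g = 0: (0.025896 + 0.008) × 0.45 = 0.01525, SE 0.1235, ratio 2.834.

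**The plan's figure first, then 7 df** (noncentral t for the t references, same SEs):

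| Reference | r_g = 0.35 | r_g = 0 |
|---|---|---|
| Normal (1.96) | 84.1% | 80.9% |
| t, 448 df (individuals) | 84.0% | 80.7% |
| t, 7 df (2.365) | 71.9% | 68.2% |

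The first two rows bracket the stated 82%. If ρ played no part in the DID, the SE would be 0.1082 and the normal power 89.9%, so ρ was most likely carried in.

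**Detectable effect.** Power of 82% on 7 df needs a ratio of 3.358. Then 3.358 × 0.1183 = 0.397 and 3.358 × 0.1235 = 0.415.

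**Sensitivity to r.** At r = 0.50 and ρ = 0.004, power on 7 df is 82.3% (r_g = 0.50) or 76.4% (r_g = 0).

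**Other scale for the effect size.** In change-score SD units, with the design effect, Var = 1.196 × (1/200 + 1/250) = 0.01076, SE 0.1037, ratio 3.374. Power is 82.3% on 7 df and 92.1% with the normal reference. r does not enter.

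**Cost of omitting park-by-time variance.** The test would use SE 0.1082 when the true SE is 0.1183 or 0.1235. Two-sided type I error is 2[1 − Φ(1.96 × 0.1082/0.1183)] = 7.3%, or 8.6% with 0.1235 in the denominator.

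**The case against.** The strongest reply is that the protocol never says how the 82% was obtained. The SD behind the effect size is undefined, and in change-score units a 7-df test gives 82.3%, nearer to 82% than either normal variant. This stands as a limit: a reader might infer that the figure can come only from a normal reference, and the document does not prove that. The reading is less natural, because it leaves r unused although the section names r as a design feature and gives it a lower bound.

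Second, 68–72% uses the least favourable r and ρ the plan allows, and completers only. That also stands. A mixed model on all available data from 620 at baseline (compound symmetry, r = 0.35, planned attrition) gives 71.5–75.4% on 7 df, and covariates may add precision. So 68–72% is a floor at the bounds and not the exact power of the planned analysis. The same allowances raise the normal-reference figure to 83.8–87.0%, so the gap remains.

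Third, a reader might infer that the written model has no park-by-time term. The text does not support this. The random effects carry no time index, and a constant park intercept would cancel from a DID. However, they multiply a vector indexed by park and time, clustering is mentioned, and the terms are given as a minimum. The form names no such effect but does not exclude one, and the detail may sit in an analysis plan that is not shown.

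Fourth, a reader might take the 9.1% tail probability of t on 7 df beyond 1.96 as the type I error when park-by-time variance is estimated. For an ordinary mixed model with the variance bounded at zero, simulation at the plan's r and ρ gives roughly 5–6%. The 7–9% applies only if that variance is left out.

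**Conclusion.** The concern holds in a conditional form. With the effect size in outcome-SD units, r = 0.35, ρ = 0.004 and 50 completers per park, the stated 82% matches a normal or individual-level reference. On the 7 df that follow from nine assigned neighborhoods, power is about 68–72%, some 10 to 14 points lower, and the effect detectable with 82% power is 0.40–0.42 instead of 0.35. Power rises with r. The change-score reading would restore 82% at r = 0.35, but only by setting aside an input that the plan states.

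The extension of DID power to Hypotheses 3, 5 and 6, with Hypothesis 3 counted twice, is an inconsistency that depends on none of these assumptions.

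**What to change.** In the Sample size section:

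- State which SD standardises the effect size, and the reference distribution and df.
- If it is the outcome SD, restate power as about 68–72% at r = 0.35 and ρ = 0.004 using t on 7 df, or give the detectable effect as 0.40–0.42 at 82% power. If the change-score SD was meant, say so and explain what role r plays.
- Limit the power statement to the INT-versus-CNT DID hypotheses, remove Hypotheses 3, 5 and 6 from it, and correct the double listing of Hypothesis 3.

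In the mixed model, here or in the analysis plan, name a park-by-time random effect and test GROUP×TIME with small-sample df. This guards against the 7–9% type I error that follows if the variance is omitted.

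The cost is wording and a less favourable stated power, with no added participants. Keeping 82% on 7 df at the bounding inputs would instead need about 69 analysed per park (621) if r_g = 0.35, or 81 per park (729) if r_g = 0.

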### Intervention and control parks

Both INT and CNT parks were selected from the same pool of designated ‘Community Open Spaces’ by the City of Detroit Parks & Recreation Department (DPRD). These parks are not maintained as traditional parks and are only mowed once annually. From this pool, we selected CNT parks matched to INT parks based on neighborhood conditions: blighted buildings, greenery, vacant lots, major roads, industrial land use, poverty, and violent/property crime.

#### Intervention description

To combat problems with severe population decline, abandoned and demolished buildings, and huge numbers of unmaintained parks and empty lots [52], DPRD created an Improvement Plan in 2017 to: 1) improve existing parks; 2) strengthen neighborhoods through parks; and 3) convert open spaces into forest buffers, meadows or urban agriculture. DPRD has now implemented this urban rejuvenation effort in partnership with Detroit Audubon.

By restoring unused parks to meadows with native grasses and wildflowers, Detroit Audubon intends to create what it calls *Detroit Bird City*, a city-wide habitat corridor to help conserve hundreds of North American bird species that pass through Michigan using the Detroit River as a migration flyway. Detroit Audubon is scheduled to restore these four parks in 2019–2020. Restorations will include: 1) replacing non-native plant and wildflower species with native species and removing turf and cement; 2) creating trails around each park’s perimeter; 3) adding signage in the park about these efforts; conducting 4) avian and plant biodiversity surveys at each park and 5) guided bird watching walks; and 6) holding community meetings and an annual stewardship event led by Detroit Audubon and DPRD to promote engagement. Each park intervention will be rolled out over a six-month period, including all the activities. Time from restoration to grassland maturation is estimated to be three years. Audubon, in partnership with residents (receiving a paid incentive for maintenance), will keep up these nature areas following restoration.

#### Control description

In June 2018, we conducted extensive inventories of all nine parks at baseline, evaluating the following: bird species, plant species, and maintenance and usage of parks. Each park had 8–20 bird species, with American Robin and European Starling the most common. Plant diversity was low, with many invasive species and turf grass. Broken cement and signs of dumping were common. Only one park was observed to be used by park-goers (see Fig. 2 for examples of current park conditions). We expect the CNT parks in this project to continue these conditions and to remain unmaintained (only mowed once annually) during the duration of the study.

**Fig. 2 Fig2:**
[figure not shown]
Examples (**a**-**e**) of current conditions in typical participating parks in Detroit, Michigan, U.S.A. Source: Google Street View

#### Risk of bias assessment

This study employs the Risk Of Bias In Non-randomized Studies of Interventions (ROBINS-I) tool [53] to assess risk of bias for the pre-intervention components. Specifically, we aimed to reduce bias due to confounding by: i) including a suite of potential individual-level confounders in our survey instrument (detailed below); ii) matching INT and CNT neighborhoods based on baseline area-level factors which may influence both the outcomes and the exposures of interest (detailed above); and iii) consideration of potential co-interventions that might occur (that are related to receiving the intervention and the outcomes). The potential for the intervention to lead to gentrification was identified. Specific items in the surveys will measure perceptions of gentrification and median home price in each study neighborhood will be quantified using publically available data from Redfin, a national real estate brokerage, for each time point. At the time of the intervention, bias in the classification of the intervention will be minimized by collecting objective data on: park usage, plant species, bird species, greenness and signs of care. Post-intervention bias will be assessed at the conclusion of the study.

The participants and the study staff collecting outcome data will be blinded to the condition assignment. This will be accomplished by referring to neighborhoods using a three-letter code and restriction of information about the intervention locations. We will assess blinding at the end of each field season by asking staff which neighborhoods they believe are receiving the intervention. Success will be determined as either i) a majority of “don’t know” responses; or ii) a balance between correct and incorrect responses. Because this is a natural experiment and the researchers have no control over whether the intervention is carried out completely in all locations and to what degree the intervention is discussed throughout the neighborhoods, assessment of blinding of participants is not appropriate.

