### Stress measures (secondary outcome)

We will measure salivary cortisol, perceived stress and anxiety. Stress alters the dynamics of the diurnal rhythm of cortisol secretion, and people who are chronically stressed exhibit lower morning and higher evening concentrations, yielding flattened slopes [19, 20, 47, 62–67]. Samples will be collected using the passive drool method [68] at waking, and 12-h after waking to permit calculation of time point concentrations and the slope of cortisol from waking to evening. The saliva collection kit contains collection supplies, a response sheet and reminder instructions. Participants will be reminded to take and freeze samples at designated times the day before their scheduled health appointment via StANDApp and/or text. Participants will also be reminded to bring kits to their appointment the next day [69, 70]. In the field, samples will be stored in a manual-defrost freezer and shipped on dry ice (once per measurement period) to Northwestern University’s Laboratory for Human Biology Research where they will be thawed, centrifuged and the supernatant aliquoted into replicate samples in smaller tubes and analyzed in duplicate. Low, medium, and high concentration controls will be prepared in at t = 0 for use throughout the study to monitor inter-assay variability. Cortisol will be measured using the Salimetrics ELISA kit as per manufacturer’s instructions [71].

We will also use two stress indicators via the survey, including: 1) Anxiety and Depression, measured via NIH’s Adult PROMIS-29 Profile v2.0 [72, 73]; and 2) the Perceived Stress Scale [74], comprising 10 items (e.g., feeling nervous) measured on Likert-type scale (0 = low, 40 = max stress). The perceived stress scale has been validated in multiple populations, and the face validity and scale content were ranked high with a Kaiser-Meyer-Olkin coefficient of 0.82 [75]. The scale’s internal consistency reliability was good in multiple languages and convergent validity was supported by expected relationships with other mental health measures, including anxiety and depression [76]. The PROMIS-29’s (our measures of anxiety and depressive symptoms) internal consistency for sub-domains has been shown to be high (Cronbach’s α > 0.88), with adequate structural validity for most domains (CFI > 0.95, RMSEA < 0.05) [77].

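### The plan says participants are blinded to condition, but the intervention is visible and publicised where they live and their blinding is never checked; self-reported outcomes should be treated as unblinded

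*Protocol article*

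**What the plan says.** In the protocol article, under Risk of bias assessment, the claim is unqualified: "The participants and the study staff collecting outcome data will be blinded to the condition assignment". The mechanism follows: "This will be accomplished by referring to neighborhoods using a three-letter code and restriction of information about the intervention locations". For staff there is a check: "We will assess blinding at the end of each field season by asking staff which neighborhoods they believe are receiving the intervention". For participants there is none. The section says that the researchers do not control how completely the intervention is delivered or "to what degree the intervention is discussed throughout the neighborhoods", and concludes that "assessment of blinding of participants is not appropriate".

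The Intervention description lists what happens at the restored parks. Besides replanting and trails, it includes "adding signage in the park about these efforts", guided bird walks and "holding community meetings and an annual stewardship event led by Detroit Audubon and DPRD to promote engagement". Residents are paid to help with upkeep afterwards.

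On outcomes, Stress measures (secondary outcome) says of the non-cortisol measures: "We will also use two stress indicators via the survey". These are the Perceived Stress Scale and the PROMIS-29 anxiety and depression items. The Survey section has participants fill in the questionnaire themselves, at home.

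**The concern.** Blinding is listed among the measures against bias, so a reader will credit it. A code on study paperwork can hide a neighborhood's arm from an analyst or an office worker. It cannot hide a replanted, signed and promoted park from someone who lives nearby.

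What is at stake is how the self-reported results are read. For a questionnaire, the participant is the outcome assessor. If people in restored-park neighborhoods answer differently because they know that their area was chosen for improvement, that shift arises after restoration and in one arm only. The difference-in-differences contrast would count it as effect, and adjustment for baseline characteristics would not remove it. A bias judgement at study end that took the blinding sentence at face value would understate this risk.

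**Working it through.** No figure is attached to the blinding claim, so there is nothing to recompute. The check sets the sections of the protocol article beside one another.

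1. **Could participants be unaware?** Participants live within 0.5 km of a study park (Participants). Restored parks get signs, trails, planting, walks, meetings and a yearly event (Intervention description). Control parks are expected to stay as they were, mown once a year (Control description). The difference between arms is therefore public and local. Hypotheses 3 and 6 also rely on residents seeing and hearing the park, so the design depends on many of them noticing the change.

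2. **Does the stated mechanism address this?** Coded names and restricted site information control what the study team says. They do not control what the restoring organisation and the city post and announce on site, which is part of the intervention.

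3. **Is the claim tested?** For staff, yes, every season. For participants, no. The reason given (uncontrolled local discussion) is itself a reason to doubt the claim. The section explains why there is no test but leaves the claim standing.

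4. **Which staff can be blinded?** Three groups need separating:
   - *Staff taking health measurements.* Appointments are at the study office (Participants; Measurement protocol), so some may stay unaware, and the season-end check applies to them.
   - *Staff visiting homes.* They go into each neighborhood to recruit, and equipment is delivered at later time points. The article calls both these staff and the health measurers field staff and does not say whether they are the same people. Their blinding is doubtful but not disproved.
   - *On-site park raters.* Graduate students record park use and signs of care at the park (Park observations and imagery). They necessarily see the restoration.

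5. **Which outcomes are exposed?**

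| Outcome | How measured | Exposure to participant awareness |
|---|---|---|
| Total activity counts (primary) | Accelerometer | Low for reporting; behavior and belt wear could still respond |
| Cortisol, CRP, A1C | Laboratory or test-strip assay | Low |
| Perceived stress, anxiety (Hypothesis 4) | Self-completed survey | Direct |
| Depression symptoms (not named in Hypothesis 4) | Self-completed survey | Direct |

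Hypothesis 4 names three indices: cortisol, perceived stress and anxiety. Two of the three are self-reported.

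**The case against.** The strongest reply is that the section largely discloses the limit. It admits that local discussion is uncontrolled, and what it says is blinded is allocation, not sight of the park. A resident may see a restored park without knowing that the study has two arms. Awareness is also partly the intervention: signs and events are components, and visual contact is a hypothesised pathway, so a change in perceived stress after seeing a better park is not simply bias. Finally, no analysis depends on blinding, and the post-intervention bias rating is still to come.

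Much of this stands, and it narrows the point. The concern is knowledge of condition or study purpose when answering, not enjoyment of the park. It does not rescue an unqualified statement that participants will be blinded. That the rating is still to come is a reason to correct the sentence now.

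Four stronger readings may tempt a reader, and the documents do not support them:

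- *That every restored-park participant knows.* At baseline only one of the nine parks was seen in use, the catchment is put at roughly a 15-minute walk, and the study expressly allows for unequal exposure.
- *That staff blinding fails as a whole.* It is checked each season and health measurements are taken at the study office. The surveys are self-completed, so staff awareness has little route into them.
- *That the bias is a given share of the powered effect.* No awareness shift appears in the documents, and the effect size of 0.35 in Sample size was drawn from literature on physical activity and cortisol, not on questionnaires.
- *That cortisol alone should carry Hypothesis 4.* This would re-rank the outcomes of a registered study. It is a debatable trade-off and does not follow from the blinding error.

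**Conclusion.** The participant-blinding statement is wrong as written. The plan's own description of the intervention makes it untenable, and the plan exempts it from any test. The reach is limited: it bears directly on perceived stress and anxiety, two of the three Hypothesis 4 indices, and on depression symptoms. It leaves the primary accelerometer outcome and the assays largely untouched. The size of any bias cannot be stated from the documents, and its presence is a risk, not an established fact. The conclusion assumes only that a meaningful share of people living within 0.5 km will notice or hear of a restoration that is signed, promoted and partly maintained by residents. It should be corrected before the end-of-study bias assessment relies on it.

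**What to change.** - **Risk of bias assessment.** Replace the blinding sentence with a statement that participants are not blinded, because the restoration is visible and publicised where they live. Limit the blinding claim to staff taking health measurements, subject to the season-end check, and say that on-site park raters are excluded.
- **Post-intervention ROBINS-I assessment.** Rate perceived stress and PROMIS anxiety and depression as measured by unblinded participants.
- **Reporting of Hypothesis 4.** Present perceived stress and anxiety beside cortisol with that caveat. Note that awareness of the park is partly the intended exposure. Leave the ranking of the outcomes unchanged.

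No new data, analysis or redesign is needed. The cost is a slightly less favourable risk-of-bias statement.
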